## Abstract

**Background:**

Intraoperative blood pressure (BP) is a concern in daily clinic anesthesia and contributes to the differences in clinical outcome. We conducted a randomized controlled trial (RCT) to compare the effect of high vs. low mean arterial pressure (MAP) levels on clinical outcomes and complications in elderly patients under general anesthesia (GA).

**Methods:**

In this multicenter, randomized, parallel-controlled, open-label, assessor-blinded clinical trial, 322 patients aged more than 65 years will be randomized for a low-level MAP (60–70 mmHg) or high-level MAP (90–100 mmHg) during non-cardiothoracic surgery under GA. The primary outcome will be the incidence of postoperative delirium. The secondary outcomes will include the delirium duration days, intraoperative urine volume, intraoperative blood loss, specific postoperative complications, and all-cause 28-day mortality.

**Discussion:**

Results of this trial will help clarify whether BP management is beneficial for elderly patients under GA and will make clear whether the effect of high-level MAP can reduce the postoperative complication compared to low-level MAP.

**Trial registration:**

ClinicalTrials.gov, NCT02857153. Registered on 15 July 2016.

**Electronic supplementary material:**

The online version of this article (doi:10.1186/s13063-017-2233-8) contains supplementary material, which is available to authorized users.

## Background

Population ageing worldwide is rapidly accelerating from 461 million people aged over 65 years in 2004 to an estimated 2 billion people by 2050 [1, 2]. Many studies in elderly persons show an association between the presence of low blood pressure (BP) and adverse outcomes, including increased cognitive impairment [3, 4], risk of dementia [5], and mortality [6, 7]. Periprocedural BP could have been influenced by anesthetic management and contributed to the differences in clinical outcome [8–12].

Hypotension has the potential to cause an ischemia-reperfusion injury which may manifest as dysfunction of any vital organ. Among the most sensitive organs to be affected in this way are the brain, kidney, and heart. Low intraoperative mean arterial pressure (MAP) is associated with increased postoperative delirium [13], risk of stroke [14], acute kidney injury [15], myocardial infarction [15, 16], and 30-day mortality [17–20]. In 101 femoral neck fracture patients aged more than 65 years under spinal anesthesia, patients who developed postoperative delirium (PD) had perioperative falls in BP after surgery [13]. A MAP < 60 mmHg and a relative decrease in MAP of 40% or more from the pre-induction BP is associated with postoperative myocardial injury if the decrease persists for more than 30 cumulative minutes [16]. MAP < 55 mmHg was associated with the development of postoperative acute kidney and myocardial injuries [15]. Terri et al. reported that a significantly increased risk of 30-day mortality with a MAP ≤ 49 mmHg or MAP decreased to more than 50% from baseline for ≥ 5 min [18].

An important aspect of intervention to decrease postoperative complications is intraoperative BP management under general anesthesia (GA). Hypotension is recognized as an important factor in postoperative complications, but what BPs are unsafe is unclear in elderly patients. We designed this study to conduct a randomized controlled trial (RCT) to compare the effect of high vs. low MAP level on clinical outcomes and complications in elderly patients under GA.

## Methods

### Trial design

This will be a multicenter, open-label, prospective RCT. Elderly patients will be included from seven centers, including Shenzhen People’s Hospital affiliated to Jinan University, West China Hospital affiliated to Sichuan University, The Affiliated Hospital of Guizhou Medical University, Taihe Hospital affiliated to Hubei University of Medicine, The Third Affiliated Hospital of Kunming Medical University, Sichuan Provincial People’s Hospital, and Henan Provincial People’s Hospital. All participants provided their written informed consent to participate in a RCT that examined the effects of low-level MAP (60–70 mmHg) vs. high-level MAP (90–100 mmHg) in elderly patients (aged 65 years or more) during non-cardiothoracic surgery under GA (trial registered at ClinicalTrials.gov under registration number: NCT02857153). MAP was calculated from the standard equation MAP = (2/3) diastolic blood pressure (DBP) + (1/3) systolic blood pressure (SBP) (in mmHg). We hypothesize high-level BP of the intervention for reducing the incidence of postoperative complications.

This study protocol was written in accordance with the Standardized Protocol Interventions: Recommendations for Interventional Trials (SPIRIT) 2013 Statement (see Additional file 1 for the completed SPIRIT checklist) [21]. The time schedule of enrollment, assessment, interventions, and follow-up according to SPIRIT guidelines can be found in Fig. 1.

**Fig. 1 Fig1:**
[figure not shown]
The schedule of enrollment, interventions, and assessments

### Patient population and eligibility criteria

Patient eligibility is assessed at the preoperative anesthesia consultation. All eligible patients must sign a specifically designed informed consent form.

Inclusion criteria are: men and women; American Society of Anesthesiologists (ASA) I–II; aged 65 years or more; scheduled to undergo non-cardiothoracic surgery with GA; and 2 h or more of scheduled surgery time.

Participants will be excluded if they meet any of the following conditions: (1) the patient suffered from cardiovascular disease and metabolic diseases, such as hypertension, cardiac diseases, diabetes; (2) the patient has severe liver, kidney, or blood disease; (3) the patient is accompanied severe cognitive impairment (Mini-Mental State Examination [MMSE] score < 15) [22]; (4) preoperative history of schizophrenia, epilepsy, parkinsonism, use of cholinesterase inhibitor, or levodopa treatment; use of haloperidol or other neuroleptics during or after anesthesia; (5) neurosurgery; (6) individuals unlikely to survive for > 24 h; (7) previous participation in this study.

Trial schematic diagram is shown in Fig. 2.

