### Randomization and blinding

Once consent is provided, participants will be assigned by the research assistant to either the low-level MAP group or high-level MAP group according to a random allocation sequence. An online random list generation will be utilized to perform blocked randomization in a 1 : 1 ratio. Trials cannot be blinded to anesthesiologist because anesthesiologist must know the MAP target to which each participant has been assigned in order to make the proper adjustment in the therapy to achieve 60–70 mmHg or 90–100 mmHg MAP. Outcome assessment and statistical analyses will be performed by independent researchers. Outcome assessor and the surgical team will be blinded to the study allocation status of participants.

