### Study outcomes

Primary outcome measure:

The incidence of PD within the seven-day period after surgery. Patients will be assessed for delirium with the CAM-ICU twice daily (at 08:00–10:00 and 18:00–20:00) during the first seven days after surgery.

Secondary outcomes:Delirium duration days during the seven-day period after surgery.Intraoperative urine volume.Intraoperative blood loss: estimated using loss of red cell mass, which was derived from differences in pre- and postoperative hematocrits and transfused red cell mass with the following equation [30]: loss of red cell mass (mL)  =  estimated blood volume of patient (mL)  ×  (preoperative hematocrit (%) − immediate postoperative hematocrit (%))/100 + (transfused packed RBCs [unit]  ×  213  ×  0.7) (estimated blood volume of patient [mL]  =  75 mL/kg for men or 65 mL/kg for women  ×  body weight [kg]; 213 mL for average volume of packed RBC; 0.7 value for hematocrit of packed RBCs).Specific postoperative complications within the seven-day period after surgery, including in bleeding requiring intervention, arrhythmias, pulmonary embolism, deep venous thrombosis, acute liver failure, acute kidney injury, acute myocardial infarction, cerebrovascular accident, or transient ischemic attack.All-cause 28-day mortality.

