### Withdrawal and dropout

Participation in the study will end at any stage if the patient refuses to continue, withdraws consent, or violates inclusion or exclusion criteria or the trial protocol. The trial will be stopped if the principle investigator believes that there are unacceptable risks of serious adverse events. No interim analysis will be conducted; however, the Data Safety and Monitoring Committee (DSMC) will perform regular reviews of all study outcome and adverse event data to ensure that there is no difference in rates of hospitalization or exacerbation in either group. The DSMC will determine final criteria for early study termination, which may be based on clear-cut evidence of worsened safety in one of the trial arms, and in the case of evidence beyond reasonable doubt of clear-cut benefit in the primary outcome measure, an effect size which would change clinical practice in the presence of the current literature and understanding of the disease area.

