### Statistical analysis

Postoperative delirium is a frequent complication after major surgery in elderly patients and is related to an increase in mortality [31]. Probability of first postoperative day PD in elderly hip fracture patients is in the range of 20–60% [9]. PD occurred in 44% of elderly patients after a major operation [31]. Our sample size was calculated to detect a 15% difference in PD between the two groups with a two-tailed test, a significance level (alpha) of 5%, and a power of 80%. The sample size calculation was performed on STATA 14.0 software (StataCorp, College Station, TX, USA). We plan to include a total of 322 participants.

Analyses will be conducted at the Clinical Research Institute of Shenzhen People’s Hospital by blinded biostatisticians. Data analysis is on an intention-to-treat basis.

The level of significance was set at 5% and statistical analysis was performed using GraphPad Prism version 6.02 for Windows (GraphPad Software, San Diego, CA, USA). Continuous variable will be summarized using means and SDs (normally distributed data) or medians and ranges (non-normally distributed data). We will perform group comparison by using the Student’s t test or Mann–Whitney test for quantitative variables and Pearson’s chi-squared test for categorical variable. The odds ratio and 95% confidence interval will be computed with logistic regression.

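### Neuroleptic use during or after anesthesia is an exclusion criterion that can end a randomized patient's participation, in conflict with the intention-to-treat statement

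*Protocol article*

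**What the plan says.** Five statements in the protocol article bear on the point.

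- **Patient population and eligibility criteria**, timing: "Patient eligibility is assessed at the preoperative anesthesia consultation".
- **Same section**, exclusion criterion (4): after a list of preoperative history items, and set off by a semicolon, it adds "use of haloperidol or other neuroleptics during or after anesthesia".
- **Randomization and blinding**, on allocation: "Once consent is provided, participants will be assigned by the research assistant to either the low-level MAP group or high-level MAP group".
- **Withdrawal and dropout**, on leaving the trial: "Participation in the study will end at any stage if the patient refuses to continue, withdraws consent, or violates inclusion or exclusion criteria". The sentence goes on to include violation of the protocol itself.
- **Statistical analysis**: "Data analysis is on an intention-to-treat basis".

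The primary outcome, under Study outcomes, is "The incidence of PD within the seven-day period after surgery", assessed by CAM-ICU twice daily. Secondary outcomes include days of delirium over the same week and all-cause mortality at 28 days.

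**The concern.** An exclusion criterion should be decidable before allocation. This one is not: whether a patient receives a neuroleptic during or after anesthesia is known only once the patient has been randomized and treated. The withdrawal rule turns it into a ground for ending participation.

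The choice of event makes this more than untidy drafting. The article does not say why neuroleptics would be given after surgery. It is clinically plausible that many would be given for delirium or agitation. If so, leaving the trial depends on the primary outcome, and the patients who leave are disproportionately delirium cases.

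Two things are then at stake:

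- **Follow-up.** Once participation ends, later CAM-ICU assessments, the count of delirium days and 28-day vital status are lost.
- **Primary comparison.** If these patients are also left out of the analysis, delirium incidence is understated in both arms. If removal differs by arm, the treatment comparison is distorted.

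**Working it through.** **1. Order of events.** Eligibility is assessed at the preoperative consultation, allocation follows consent, and anesthesia follows allocation. Neuroleptic use during or after anesthesia therefore comes after randomization. Under the withdrawal rule, a randomized patient given such a drug on, say, day 2 meets an exclusion criterion and participation ends. Under the intention-to-treat statement, the same patient belongs in the analysis. The article does not say which statement governs.

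**2. The plan's own sample size.** The stated target reads "detect a 15% difference in PD between the two groups with a two-tailed test, a significance level (alpha) of 5%, and a power of 80" percent, with 322 participants in 1:1 allocation. The article cites a delirium rate of 44% after major surgery. I assume this was the planning rate, so 44% vs 29%.

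n per arm = [z(0.975)·√(2p̄(1−p̄)) + z(0.80)·√(p₁(1−p₁) + p₂(1−p₂))]² / (p₁−p₂)², with p̄ = 0.365

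= (1.3344 + 0.5660)² / 0.0225 = 160.5, rounded up to 161 per arm, or 322 in total.

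The stated figure is reproduced. Power with 161 per arm is 80.1%, with no allowance for post-randomization removals.

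**3. Worst-case effect of removal.** Suppose a fraction f of delirious patients in an arm receives a neuroleptic and is deleted from numerator and denominator, recorded events included. The article gives no value for f, so every f below is an assumption.

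Observed rate = p(1−f)/(1−pf); patients left = 161(1−pf).

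For f = 0.25, low MAP: 0.44×0.75/(1−0.11) = 0.371, with 143.3 patients left. High MAP: 0.29×0.75/(1−0.0725) = 0.2345, with 149.3 left.

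| f, low / high MAP | Observed rates | Difference (points) | Odds ratio | Power |
|---|---|---|---|---|
| 0 / 0 | 44.0% vs 29.0% | 15.0 | 1.92 | 80% |
| 25% / 25% | 37.1% vs 23.5% | 13.6 | 1.92 | 72% |
| 50% / 50% | 28.2% vs 17.0% | 11.2 | 1.92 | 59% |
| 30% / 10% | 35.5% vs 26.9% | 8.6 | 1.50 | 36% |
| 10% / 30% | 41.4% vs 22.2% | 19.2 | 2.47 | 95% |

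Equal removal leaves the odds ratio unchanged because the odds in each arm are multiplied by the same factor (1−f). The risk difference and power still fall. Unequal removal biases the odds ratio, in either direction. The 95% in the last row reflects an inflated effect and is not a gain.

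**4. No true effect (44% in both arms).** The rejection probability is that of a two-sided 5% test given the spurious difference and its standard error.

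| f, one arm / other arm | Observed rates | False difference (points) | Standard error (points) | Rejection |
|---|---|---|---|---|
| 30% / 10% | 35.5% vs 41.4% | 5.9 | 5.67 | about 18% |
| 60% / 40% | 23.9% vs 32.0% | 8.1 | 5.64 | about 30% |

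**The case against.** **Removal from the analysis is nowhere stated.** A reader might infer that delirium cases are dropped from the comparison and that intention-to-treat has become impossible. The text does not support that. The withdrawal rule ends participation; it does not say that data already collected are discarded, and the analysis is declared to be by intention-to-treat. If the neuroleptic is a response to delirium and CAM-ICU was already positive, the event is on record and can count. On that reading, incidence suffers only for patients given the drug before any positive assessment. This objection stands, and it makes the tabulated figures a worst case. It does not rescue delirium duration or 28-day mortality, because observation after removal is lost whatever the analysis is called.

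**The removal fractions are invented.** Also true. The article gives neither the frequency of neuroleptic use nor the reason for it, and the false-positive rate depends heavily on the assumed gap between arms.

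**Blinding limits differential removal.** The surgical team and the outcome assessor are blinded, which makes a different readiness to treat on the ward less likely. It does not rule out unequal removal. The anesthesiologist is unblinded and the clause also covers use during anesthesia. Delirium severity could itself differ by arm if the MAP target affects it.

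**Perhaps only planned use was meant, or the article abbreviates.** The text says use, not planned use. If planned use was intended, the wording still needs correcting. The criterion is stated, so this is not a matter of condensed detail.

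**Conclusion.** The conflict in the text is clear. An exclusion criterion names a post-randomization event, the withdrawal rule acts on it, and the intention-to-treat statement points the other way.

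The bias is a risk created by that conflict, not a certainty. It rests on two assumptions: that postoperative neuroleptics are given largely for delirium or agitation, and, for bias in incidence, that sites or analysts drop these patients or that the drug precedes the first positive CAM-ICU. Loss of later follow-up needs only that the withdrawal rule is applied as written.

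The worst-case calculations show that the matter is not trivial: power of 59% to 72% under equal removal of 50% to 25%, and false-positive rates of about 18% to 30% under the unequal removals shown. They do not estimate what will happen in this trial. Nothing in the article shows that any patient has been removed on this ground.

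The point should be settled before recruitment goes much further, because assessments missed after removal cannot be recovered in the analysis.

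**What to change.** Reconcile the three sections by amendment:

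1. Limit the exclusion criteria to facts known before randomization, so that neuroleptic use after randomization is not a ground for ending participation.
2. State that every randomized patient stays in CAM-ICU and 28-day follow-up, and in the primary intention-to-treat analysis, whatever neuroleptic is given.
3. Record neuroleptic use as a post-randomization variable.
4. For any enrolled patient already removed on this ground, keep the collected data in the analysis and resume follow-up where the window is still open. The article reports 60 recruited by 1 November 2016, so this is worth checking now. CAM-ICU assessments missed in a closed seven-day window cannot be restored.

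This does not judge which drugs clinicians may give. The cost is a short amendment with the approvals listed under Protocol amendments (steering committee, DSMC, sponsor, funder, then ethics). No added patients are needed. The additional work is recording neuroleptic use and completing the scheduled follow-up of patients who would otherwise have been withdrawn.

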**Fig. 2 Fig2:**
[figure not shown]
Trial flow chart

### Randomization and blinding

Once consent is provided, participants will be assigned by the research assistant to either the low-level MAP group or high-level MAP group according to a random allocation sequence. An online random list generation will be utilized to perform blocked randomization in a 1 : 1 ratio. Trials cannot be blinded to anesthesiologist because anesthesiologist must know the MAP target to which each participant has been assigned in order to make the proper adjustment in the therapy to achieve 60–70 mmHg or 90–100 mmHg MAP. Outcome assessment and statistical analyses will be performed by independent researchers. Outcome assessor and the surgical team will be blinded to the study allocation status of participants.

### Intervention

On the day of surgery, patients come to the operating room and are provided with standard monitoring (electrocardiogram, oxygen saturation, non-invasive blood pressure, and invasive pressure monitoring). GA is given using midazolam (0.04 mg.kg^–1^) and propofol (as deemed appropriate by the anesthesiologist), opioids (fentanyl 3–6 μg.kg^–1^ and remifentanil 0.1–0.5 μg.kg^–1^.min^–1^), muscle relaxants (cisatracurium/rocuronium), and maintained with sevoflurane with inhaled concentrations of 1.5% sevoflurane in oxygen. Supplemental dosing of 1 μg.kg^–1^ of fentanyl is used every hour from induction up to approximately 1 h prior to the end of surgery. A tramadol bolus of 2 mg.kg^–1^ is given 15–30 min before the end of surgery. Propofol infusion is stopped 5–10 min before the end of surgery, whereas at the end of skin closure, remifentanil was discontinued.

According to grouping, MAP is regulated to the goal level (60–70 mmHg or 95–100 mmHg) during GA. If necessary, intravenous anti-hypertensives (urapidil [0.2–0.5 mg.kg^–1^] or phenylephrine [4–6 μg.kg^–1^] when MAP exceeds 10 mmHg of the target value), rather than more anesthesia, may be used in situations wherein sympathetic stimulation is high; yet a sufficient amount of anesthesia is administered and bispectral index (BIS) shows an adequate depth of hypnosis. Sedation is provided by a propofol infusion targeted to a BIS number of approximately 50 during GA. Atropine (5–10 μg.kg^–1^) and esmolol (1–3 mg.kg^–1^) would be used at the time of heart rate < 50 beats.min^–1^ and > 110 beats.min^–1^, respectively.

Lactated Ringer’s solution is given to bring the maintenance fluids to 10 mL.kg^–1^.h^–1^ [23]. Blood loss could be corrected for in a 1 : 1 ratio using gelofusine. Hospital transfusion guidelines are used to determine whether blood products are necessary (hemoglobin [HB] level < 10 g.dl^–1^ in patients with cardiac co-morbidities and < 7 g.dl^–1^ in those without cardiac disease). For later starting cases, an additional bolus of Ringer’s solution of 1.5 mL/kg/fasted hour from 08:00 _i_s given to bring the total to 2 mL/kg/fasted hour. If urine output decreases to < 0.5 mL.kg^–1^.h^–1^ for 1 h, fursemide 0.3 mg.kg^–1^ is given.

Mechanical ventilation patterns are adjusted to obtain an end-tidal carbon dioxide value of 35–45 mmHg at 5–10 min after induction of anesthesia.

For patients with endotracheal tubes, intravenous sedatives including propofol or midazolam were administrated continuously and titrated by bedside nurses to a target sedation level (Richmond Agitation Sedation Scale [RASS] range, – 2 to + 1) [24]. Daily awakening is used for those who were not extubated in the morning.

All patients receive patient controlled intravenous analgesia (PCIA) during postoperative days 1–3. Patients would be given PCIA with fentanyl 5 μg.mL^–1^, tramadol 5 mg.mL^–1^, and tropisetron 50 μg.mL^–1^. The PCIA is programmed to deliver a bolus dose of 2 mL, with background infusion of 2 mL/h and a lockout of 5 min, with a 1-h limit of 10 mL.

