### Data collection

We will collect outcomes relating to four levels of specification of outcome measures as proposed by Zarin et al. [25]: domain (for example, postoperative delirium); specific metric (for example, RASS); specific metric used to characterize each participant’s results (for example, the incidence within the seven-day period after surgery); and method of aggregation (for example, mean change and 95% confidence interval).

A research assistant will collect date elements from patient medical records, including:

Demographic data:> data of birth;> gender;> preoperative diagnosis;> previous treatments;> co-morbid conditions;> preoperative vital signs: pulse (P), BP, respiratory rate (R);> baseline laboratory tests: aspartate transaminase (AST), alanine aminotransferase (ALT), blood urea nitrogen (BUN), serum creatinine (CREA), C-reactive protein (CRP), creatine kinase (CK), creatine kinase isoenzymes (CK-MB), brain natriuretic peptide (BNP), HB, white blood cell (WBC), platelet (PLT), oxygenation index (PaO_2_/FiO_2_), arterial carbon dioxide pressure (PaCO_2_), total bilirubin and fractions, prothrombin time (PT), activated partial thromboplastin time (APTT), international normalized ratio (INR);> preoperative electrocardiogram;> the ASA classification for preoperative health assessment of surgical patients [26].

Operative information:> name of surgical operation;> participation of fellow, resident, or medical student/clinical clerk in the surgical team;> intraoperative blood loss;> transfusion of blood products (packed red blood cells, platelets, fresh frozen plasma, albumin) and number of units;> volume of intravenous crystalloid infusion;> intraoperative urine volume;> intraoperative drug dosage, including in urapidil, phenylephrine and fursemide;> duration of surgery (defined as the number of hours between skin incision and closure of skin).

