### Trial status

The trial is currently recruiting participants. To date (1 November 2016), 60 participants have been recruited. A report releasing study results will be submitted for publication in an appropriate journal, approximately 15 months after finishing data collection.

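### The only drug rule triggered by MAP lists phenylephrine, a vasopressor, as an anti-hypertensive for pressure above target, and nothing else in the article gives its correct direction

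*Protocol article*

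**What the plan says.** The Intervention section of the protocol article opens its pressure paragraph with the general instruction that "MAP is regulated to the goal level" of the assigned arm during anesthesia. The next sentence names the drugs: "intravenous anti-hypertensives (urapidil [0.2–0.5 mg.kg^–1^] or phenylephrine [4–6 μg.kg^–1^] when MAP exceeds 10 mmHg of the target value". It then states when they apply: "rather than more anesthesia, may be used in situations wherein sympathetic stimulation is high", provided that anesthesia is sufficient and the bispectral index (BIS) confirms it.

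Two other places touch on this. Randomization and blinding says that the anesthesiologist must know the target in order to "make the proper adjustment in the therapy to achieve 60–70 mmHg or 90–100 mmHg MAP". Data collection lists "intraoperative drug dosage, including in urapidil, phenylephrine and fursemide" among the operative items to be recorded.

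**The concern.** Phenylephrine is an alpha-1 agonist and raises blood pressure. The sentence groups it with urapidil under one class label, one trigger and one clinical situation, all of which describe a patient whose pressure is too high. Read as printed, the rule offers a pressor to a patient who is already above target.

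The assigned MAP is the randomized intervention, and giving or withholding these drugs is one way of holding it. The sentence is therefore part of the definition of treatment in both arms, and seven centers (Trial design) have to apply it alike. Phenylephrine is also the only vasopressor that the article names, so it is the drug one would expect to support a goal of 90 mmHg or more under general anesthesia. What is at stake is clarity about how the assigned pressure is to be held, and the safety of a patient treated by someone who follows the text literally.

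**Working it through.** The plan gives no figure on this point, so there is none to reproduce. The check is a reading of every drug or fluid rule in the Intervention section, and of every place that might correct the rule. The one outside input is general pharmacology: urapidil lowers blood pressure and phenylephrine raises it.

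**Step 1. Rules in the Intervention section and what triggers them**

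| Agent | Printed trigger | Triggered by MAP? |
|---|---|---|
| Urapidil 0.2–0.5 mg/kg | MAP above target by 10 mmHg | Yes |
| Phenylephrine 4–6 μg/kg | The same trigger, shared with urapidil | Yes |
| Atropine, esmolol | Heart rate below 50 or above 110 per minute | No |
| Furosemide | Urine output below 0.5 mL/kg/h for 1 h | No |
| Propofol infusion | BIS of about 50 | No |
| Ringer's solution, gelofusine, blood products | Maintenance rate and fasting time, blood loss, hemoglobin | No |

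The urapidil–phenylephrine sentence is thus the only rule that MAP triggers.

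**Step 2. Does each part of that rule fit each drug?**

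| Part of the rule | Urapidil (lowers MAP) | Phenylephrine (raises MAP) |
|---|---|---|
| Class: anti-hypertensive | Fits | Wrong |
| Trigger: MAP exceeds the target | Fits | Wrong |
| Situation: "may be used in situations wherein sympathetic stimulation is high" | Fits | Wrong |

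All three parts fit urapidil and none fits phenylephrine.

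**Step 3. Is it corrected elsewhere?** The sentence under Randomization and blinding states an aim and names no drug. The Data collection item is the only other mention of phenylephrine; it records a dose and gives no indication or direction. Neither corrects the rule.

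**Step 4. Does a charitable reading repair it?** Suppose that *exceeds* was meant as *deviates in either direction by more than*. The trigger could then cover phenylephrine for a low pressure. The class label would still call it an anti-hypertensive, and the sentence would still tie its use to high sympathetic drive. One of the three faults is removed and two remain. To get a usable rule, the reader has to change the label, widen the trigger and detach the clinical condition from one of the two drugs.

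**The case against.** The strongest reply is that this is a slip of drafting and not of design. The article's English is rough in several places, the intended meaning is fairly plain, and the sentence is permissive. The person applying it is an anesthesiologist who knows the target and would not give phenylephrine to lower a pressure. All of this stands, and it is why the point is minor. It does not make the sentence right.

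A second reply is that an article condenses the full protocol and may leave titration detail to it. That also stands, for what is missing. The absence of a printed trigger for MAP below range, and of a definition of the target value for a range, is therefore not held against the plan. But the article does print the drugs, doses, class and trigger, and for one drug the class and trigger are wrong. That is a misstatement, which condensing does not excuse.

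A reader might go further and take the 10 mmHg as a two-way margin within which nothing is done. Counted from the range bounds, the low arm would then run up to 70 + 10 = 80 mmHg and the high arm down to 90 − 10 = 80 mmHg, so the arms would meet. The low arm could also fall to 60 − 10 = 50 mmHg, although the Background reports that "MAP < 55 mmHg was associated with the development of postoperative acute kidney and myocardial injuries". The documents do not support this inference:

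- It needs an assumed two-way trigger and an assumed reference point. Counted from the midpoints, the limits would be 65 + 10 = 75 and 95 − 10 = 85 mmHg, with a low-arm lower limit of 65 − 10 = 55 mmHg.
- It treats an optional rescue rule as if it overrode the general instruction to hold MAP at the goal. Nothing says that a pressure outside the goal but within 10 mmHg of it is left alone.
- The margin would have the same consequence if the two drugs were correctly separated, so it does not measure this error.

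**Conclusion.** The concern holds as an error in one operative sentence: phenylephrine is given the wrong class, the wrong trigger and the wrong clinical situation, and no other part of the article states its correct direction. Severity is minor.

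The error has no numerical size. It does not enter the sample size or the significance level. How often anyone would act on the literal text is unknown, and probably rare. No claim is made about pressures left untreated, loss of separation between the arms, a lower MAP limit or required margins, nor about bias, power or a demonstrated safety failure.

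The conclusion rests on the text of the article and on the general fact that phenylephrine raises blood pressure. Whether the full protocol or the site instructions repeat the error cannot be seen from the article. The Intervention section's upper goal of 95–100 mmHg, against 90–100 mmHg elsewhere, is a separate inconsistency and plays no part here.

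**What to change.** Split the sentence by direction, for both arms and with the doses as printed. For example:

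> If MAP is above the assigned range although anesthesia is adequate, urapidil (an anti-hypertensive) may be given instead of deepening anesthesia. If MAP is below the assigned range, phenylephrine (a vasopressor) may be given, whether or not sympathetic stimulation is high.

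Any margin around the range remains for the trial's clinicians to set; this point does not require a particular one.

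Then confirm that the full protocol and the site instructions carry the corrected rule. If they do, correcting the published sentence is enough. If they repeat the error, make a short amendment by the route under Protocol amendments: agreement with the steering and safety committees, sponsor and funder, then ethical approval and notice to the sites.

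The cost is one sentence and a document check, with no extra patients, procedures or data. Trial status reports that "60 participants have been recruited" as of 1 November 2016, so at that date the correction could still have covered up to 322 − 60 = 262 participants. The number still to be treated later is not known from the article.
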